### Endpoints of trial

The primary endpoint of this trial will be the evaluation of the percentage of patients still alive 24 months after randomisation. The secondary endpoints for this trial include, overall survival (OS) at 36 months, disease free survival (DFS) at 24 and 36 months, R0 resection rates, treatment tolerance, postoperative mortality and morbidity evaluated by Clavien-Dindo severity index [16], rates of completion of all elements of the planned therapy, the prognostic impact of positive peritoneal cytology and the assessment of quality of life (EORTC QLC-C30 and EORTC STO 22). A complementary study, subsequently described, will assess the emotional and cognitive impact of surgery and perioperative chemotherapy for both the patient and their partner.

OS is defined as the time interval between inclusion and death from whatever cause and patients lost to follow-up will be censured at the last date of follow-up. Disease free survival will be defined as the time interval between the date of inclusion and the date of first recurrence or the date of death in the absence of disease recurrence. The R0 resection rate will correspond to the percentage of patients benefitting from a micro and macroscopically complete resection [17]. Neoadjuvant and/or adjuvant treatment tolerance will be estimated according to the National Cancer Institute Toxicity Criteria (NCI-CTC version 4.0). Evaluation of the uptake of all elements of planned treatment will be performed and quality of life questionnaires and human and social sciences questionnaires will be completed at 4 defined time-points – randomisation, the eve of commencement of treatment, 1 month (+/−7 days) after leaving hospital following surgery and 1 month (+/−7 days) after completing adjuvant chemotherapy. The quality of life questionnaires will also be completed at each 4 monthly follow-up visit.

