### Chemotherapy regimens

#### Peri-operative chemotherapy (group A)

Patients randomised to group A will receive the established European standard of treatment– 3 pre- and postoperative cycles of ECF. Neoadjuvant treatment will commence within 4 weeks of randomisation and each cycle will last 21 days. Epirubicin will be administered at a dose of 50 mg/m^2^ by intravenous infusion over 30 minutes on day 1 followed by intravenous infusion over 60 minutes of cisplatin at a dose of 60 mg/m^2^ and then continuous infusion of 5-fluorouracil from days 1–21 at a dose of 200 mg/m^2^/day. It will be permitted to replace infusion of 5-fluorouracil with its oral equivalent (capecitabine) depending on the normal treatment habits of each centre.

Patients will undergo clinical and staging re-evaluation 2–3 weeks after completion of the neoadjuvant regimen and surgical resection will be performed 3–6 weeks after the completion of neoadjuvant chemotherapy. Adjuvant chemotherapy will commence 6–12 weeks after surgery and will comprise the same regimen where there has not been disease progression or severe toxicity during the neoadjuvant phase. If either of these events has occurred the administration of the adjuvant chemotherapy or the protocol for its substitution will be left to the decision of the local multi-disciplinary team meeting. Clinical, haematological and toxicity evaluations will be carried out prior to administration of each cycle of chemotherapy and an echocardiogram will be performed prior to neoadjuvant and adjuvant treatments and at the conclusion of adjuvant treatment.

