### Reasons for discontinuing treatment protocol

The treatment protocol may be discontinued for the following reasons: decision of the treating doctor, high grade toxicity, occurrence of a serious adverse effect, disease progression, patient refusal to continue and patient death. In cases where treatment is discontinued, patients will remain within the intention to treat analysis.

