Recently Messager et al [8] have published the results of a large multicentre comparative cohort study investigating the impact of peri-operative chemotherapy on survival in patients with SRC gastric tumours. It represents the largest study conducted on this histological subtype and involved analysis of 1050 patients diagnosed with SRC gastric tumours. No survival benefit was demonstrated for patients with SRC histology receiving peri-operative chemotherapy. Nor did neoadjuvant therapy result in tumour down-staging, down-staging of nodal disease, or decrease the disease recurrence. Indeed the authors found some evidence that disease progression during neoadjuvant treatment may have occurred in this subgroup of patients - extended resections were more commonly required and a longer median survival for patients treated with surgery alone prior to the incorporation of peri-oerative chemotherapy into the French guidelines for GA in 2006. This provides a clear imperative of the assessment of an alternative treatment strategy.

As several studies [11-14] have suggested a relative chemo resistance for SRC tumours and delay in definitive surgery may favour tumour progression [8] we hypothesise that a policy of primary surgery for SRC tumours, followed by adjuvant chemotherapy, will improve overall survival at 2 years when compared to a standard peri-operative chemotherapeutic strategy. This primary outcome criteria is justified as it provides a short term evaluation criteria (important in view of the very poor prognosis associated with this disease) and survival at 24 months has been found in a multicentre retrospective series of over 1000 patients to be significantly different (27% vs. 10%) [8].

This randomised trial will provide high level evidence regarding the value of a strategy of primary surgery for SRC gastric tumours. Whilst the development of new biomarkers and associated targeted therapies are awaited to individualise gastric cancer therapy, the results of this trial should will help further in devising individualised protocols of patient care in a tumour group whose diversity increasingly demands assessment of alternative strategies.

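### Disease-free survival starts before surgery but counts only recurrence or death, so patients in either arm never cleared of tumour stay event-free until they die

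*Protocol article*

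**What the plan says.** Under Endpoints of trial, the protocol article lists "disease free survival (DFS) at 24 and 36 months" among the secondary endpoints. It then defines the measure in full: the clock starts at inclusion and stops at "the date of first recurrence or the date of death in the absence of disease recurrence". Both the start and the event list are fixed.

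Elsewhere the article treats progression as something different from recurrence:

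- In group A, the same regimen is given after surgery only "where there has not been disease progression or severe toxicity during the neoadjuvant phase".
- Reasons for discontinuing treatment protocol lists "high grade toxicity, occurrence of a serious adverse effect, disease progression, patient refusal to continue and patient death", and adds: "In cases where treatment is discontinued, patients will remain within the intention to treat analysis".
- Recurrence appears in the section on follow-up after surgery, where its site is to be recorded as loco-regional or distant.

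The Discussion gives as part of the rationale that "disease progression during neoadjuvant treatment may have occurred in this subgroup of patients". Resection radicality (R0, R1, R2) is reported under Histological analysis but is not linked to DFS. The statistical section plans a log-rank comparison of survival endpoints in phase III.

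**The concern.** The start of the clock and the event list do not fit together. At inclusion every patient has an unresected tumour. A patient who progresses before surgery, proves unresectable or metastatic, or has macroscopic tumour left behind has never been disease free, so has nothing to recur. On the literal text that patient has no event until death, yet stays in the intention-to-treat analysis.

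The two arms are exposed differently. Only group A waits through three cycles and a scheduled restaging before surgery, and progression in that interval is the harm the trial suspects. The endpoint therefore leaves out the date of a failure that the strategy comparison is meant to reveal. What is at stake is the DFS comparison, both the percentages at 24 and 36 months and the log-rank test. Overall survival is not involved.

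**Working it through.** The article gives no DFS rate, effect size or event count, so there is no stated figure to reproduce. The check has three parts.

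**1. Timelines from the protocol's own windows.** For group A, "Neoadjuvant treatment will commence within 4 weeks of randomisation and each cycle will last 21 days".

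- Chemotherapy starts at day 0-28 and lasts 3 × 21 = 63 days, so it ends at day 63-91.
- Restaging 2-3 weeks later falls at day 63 + 14 = 77 to day 91 + 21 = 112.
- Surgery 3-6 weeks after chemotherapy falls at day 63 + 21 = 84 to day 91 + 42 = 133.
- Group B is operated on by day 28.

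So A has an interval in which preoperative progression can arise and be detected; B has almost none. Unresectable disease at operation and R2 resection can occur in both arms.

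**2. Effect on 24-month DFS.** Let q be the share of an arm that progresses before surgery or is never cleared of tumour, t the month of that failure, and m the median survival afterwards (exponential). The literal definition overstates 24-month DFS in that arm by q × 0.5^((24 − t)/m). I take t = 3.5 in A and t = 1 in B from the windows above. The values of q and m are assumptions, because the documents give none.

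Share of failed patients still counted disease free at 24 months:

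- A: 0.5^(20.5/6) = 9.4% and 0.5^(20.5/12) = 30.6%
- B: 0.5^(23/6) = 7.0% and 0.5^(23/12) = 26.5%

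| q in A | q in B | m (months) | Overstated in A | Overstated in B | Net shift |
|---|---|---|---|---|---|
| 10% | 5% | 6 | 0.94 | 0.35 | 0.6 towards A |
| 10% | 5% | 12 | 3.06 | 1.32 | 1.7 towards A |
| 20% | 5% | 6 | 1.87 | 0.35 | 1.5 towards A |
| 20% | 5% | 12 | 6.12 | 1.32 | 4.8 towards A |
| 10% | 10% | 6 | 0.94 | 0.70 | 0.2 towards A |
| 10% | 10% | 12 | 3.06 | 2.65 | 0.4 towards A |
| 5% | 10% | 12 | 1.53 | 2.65 | 1.1 towards B |

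The last four columns except m are in percentage points. A simulation with 400,000 patients per arm agreed with the formula.

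**3. Effect on the hazard ratio.** This is a simulation of 314 patients (157 per arm, 1,500 runs), with log-rank estimates censored at 36 months. All its other inputs are assumptions: median DFS 8 months in A among patients cleared of disease, HR 0.70 in B against A among those patients, and failure at month 3 in A and month 1 in B.

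| q in A | q in B | m (months) | HR, failures counted | HR, literal definition |
|---|---|---|---|---|
| 10% | 5% | 6 | 0.69 | 0.71 |
| 15% | 5% | 6 | 0.66-0.67 | 0.71-0.72 |
| 20% | 5% | 6 | 0.63-0.64 | 0.71 |
| 10-20% | 5% | 12 | 0.69-0.64 | 0.74-0.80 |
| 5% | 5% | 6 | 0.71-0.72 | 0.71-0.72 |
| 10% | 10% | 6 | 0.74 | 0.73 |
| 5% | 10% | 6 | 0.76-0.77 | 0.73-0.74 |

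Ranges within a single-scenario row reflect repeated runs. With equal failure rates the definition hardly moves the HR. With more failures in B it flatters B.

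**The case against.** **Direction.** A reader might infer that the definition is known to favour group A. The documents do not support that. They give no rate of preoperative progression, non-resection or R2 resection in either arm, and the Discussion says only that progression may have occurred. R2 resection and unresectable disease also arise in B. This objection stands: the direction is probable, not established.

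**Importance.** A reader might treat DFS as the main secondary efficacy endpoint and read the lower HR contrast as lost power. The article ranks no secondary endpoint, lists overall survival at 36 months first, and claims no power for DFS. This also stands. On the 24-month percentage with 10% against 5% failing, the shift can be as small as 0.6 points.

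**Visibility elsewhere.** R0 rate, completion of planned therapy and overall survival would all show failures in A. True, but none of them corrects the DFS curve or its log-rank test.

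**Condensed article.** Event-level rules are often left to the full protocol or analysis plan. That would answer a missing detail. Here the rule is stated with its start and its events, and what is stated misclassifies patients. Nor can recurrence easily be read to include progression, since the article uses the two terms for different phases of care.

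**Asymmetric detection.** Only A has scheduled preoperative restaging, so counting progression on its actual date would introduce an arm-specific assessment time. This stands and shapes the fix.

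**Conclusion.** The DFS definition is badly fixed. In both arms, patients who progress before surgery, are unresectable or metastatic, or have an R2 resection count as disease free until death. That follows from the text alone.

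The size and direction of the effect on the comparison rest on assumptions. With 10-20% failing in A, 5% in B and a median survival of 6-12 months afterwards, 24-month DFS shifts about 0.6 to 4.8 points towards A. With the 6-month median, the HR moves from about 0.63-0.69 to 0.71. The longer preoperative interval in A and the trial's own hypothesis make this direction the likelier one. The shift all but disappears at equal failure rates and reverses if B fails more often.

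The phase II decision rule and the phase III overall survival test are unaffected. The definition should be corrected, but it does not threaten the trial's main conclusion.

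**What to change.** Define the event identically in both arms, measured from randomisation, as the first of:

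- disease progression;
- failure to achieve macroscopically complete resection (unresectable or metastatic disease at restaging or operation, no resection, or R2);
- recurrence after R0 or R1 resection;
- death from any cause.

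State how resected peri-tumoural localised carcinomatosis is classed, since the Surgical Resection section foresees it. The name event-free survival would describe the endpoint better.

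Because surgery and restaging fall at different times in the two arms, the main definition should date preoperative progression and failure to achieve resection at a common landmark after randomisation, for example 6 months, with earlier deaths counted when they occur. Six months lies beyond the latest planned surgery in A (day 133). Add a sensitivity analysis on actual dates: the landmark is a compromise, since a recurrence in B before month 6 keeps its own earlier date.

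The cost is a change of wording. Restaging, operative and pathology findings are already collected. Reported DFS will look slightly less favourable.

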### Randomisation

Randomisation will be performed by minimisation with stratification criteria – centre, tumour stage, performance status and tumour localisation. The maximum delay between randomisation and either the start of neoadjuvant treatment or surgery will be 4 weeks. A randomisation number and the treatment allocation are sent by facsimile communication by the “Centre de Randomisation-Gestion-Analyse” (CRGA) at the Fédération Francophone de Cancérologie Digestive (FFCD) headquarters in Dijon, France to the investigator after the receipt of the inclusion form.

### Pre-therapeutic work-up

Prior to inclusion in the trial an information booklet will be given to each patient and the trial protocol will be clearly explained. The initial work-up must take place in the 4 weeks preceding randomisation and will comprise of the following:

i) A complete physical examination.

ii) Estimation of full blood count, calculation of creatinine clearance using the Cockcroft formula, measurements of electrolytes, total protein, albumin, alkaline phosphatase, aspartate transaminase, alkaline transaminase, total and conjugated Bilirubin, gamma-GT, pregnancy test for females of reproductive years and discussion of contraceptive methods during the trial period.

iii) Tumour markers evaluation – carcinoembryonic antigen and carbohydrate antigen 19.9.

iv) Assessment of operability – electrocardiogram, cardiac echography, anaesthetic consultation and posterior-anterior and lateral chest x-ray (not necessary where a CT thorax has been performed).

v) Oesophago-gastro-duodenoscopy with multiple biopsies and examination by retroflexion.

vi) Contrast study.

vii) Contrast enhanced computerised tomography of the thorax, abdomen and pelvis.

viii) Endoscopic ultrasound will be performed systematically. The pre-therapeutic TNM classification will be made by EUS, except for tumours which cannot be traversed by EUS, in which case the TNM stage will be based on CT findings.

ix) Staging laparoscopy will be performed systematically. All suspicious lesions will be biopsied and a laparoscopic feeding jejunostomy will be performed for patients who have lost >10% of habitual body mass. Peritoneal fluid, if already present, will be sampled prior to any manipulation of the tumour and if the sample gives <50 mls, 100mls of normal saline will be instilled around the primary tumour and 50mls recuperated from the epigastric/left hypochondriac regions after a delay of 2 minutes without tumour manipulation. In cases of the discovery of peritoneal carcinomatosis, peritoneal cytology will not be performed.

x) Positron emission tomography scanning will not be routinely performed due to the known weak tracer uptake specific to SRC tumours [14].

### Treatment methods

The therapeutic scheme for this trial is depicted in Figure 1.

**Figure 1 F1:**
[figure not shown]
Therapeutic scheme for the protocol.

### Chemotherapy regimens

#### Peri-operative chemotherapy (group A)

Patients randomised to group A will receive the established European standard of treatment– 3 pre- and postoperative cycles of ECF. Neoadjuvant treatment will commence within 4 weeks of randomisation and each cycle will last 21 days. Epirubicin will be administered at a dose of 50 mg/m^2^ by intravenous infusion over 30 minutes on day 1 followed by intravenous infusion over 60 minutes of cisplatin at a dose of 60 mg/m^2^ and then continuous infusion of 5-fluorouracil from days 1–21 at a dose of 200 mg/m^2^/day. It will be permitted to replace infusion of 5-fluorouracil with its oral equivalent (capecitabine) depending on the normal treatment habits of each centre.

Patients will undergo clinical and staging re-evaluation 2–3 weeks after completion of the neoadjuvant regimen and surgical resection will be performed 3–6 weeks after the completion of neoadjuvant chemotherapy. Adjuvant chemotherapy will commence 6–12 weeks after surgery and will comprise the same regimen where there has not been disease progression or severe toxicity during the neoadjuvant phase. If either of these events has occurred the administration of the adjuvant chemotherapy or the protocol for its substitution will be left to the decision of the local multi-disciplinary team meeting. Clinical, haematological and toxicity evaluations will be carried out prior to administration of each cycle of chemotherapy and an echocardiogram will be performed prior to neoadjuvant and adjuvant treatments and at the conclusion of adjuvant treatment.

#### Adjuvant chemotherapy regimen - group B

Patients randomised to group B will undergo primary surgery followed by 6 cycles of adjuvant ECF chemotherapy. Primary surgical resection will take place within 4 weeks of randomisation. Six cycles of adjuvant chemotherapy will commence 6–12 weeks after surgical resection. Each cycle of chemotherapy will consist of the same regimen of ECF as used for group A and at the same dosage.

### Re-staging post neoadjuvant chemotherapy (group A)

Tumoural restaging will be performed 2–3 weeks after the end of neoadjuvant chemotherapy. It will comprise of the following examinations; clinical examination, same blood analyses as at inclusion [see *Pre*-*Therapeutic Work*-*Up* (*ii*)], tumour marker estimation (CEA and CA19.9), anaesthetic consultation, oesophago-gastro-duodenoscopy with multiple biopsies and retrovision, radiological contrast study, CT thorax, abdomen and pelvis and EUS evaluation. This re-evaluation will be performed by the same team and by the same technique as the initial work-up.

### Surgical Resection

All surgical resections will be performed by open laparotomy. At the start of definitive surgical resection, peritoneal cytology will be performed in order to study the effects of, (a) preoperative chemotherapy on the results of cytology performed during staging laparoscopy in group A and, (b) the effect on peritoneal cytology of the interval between exploratory laparoscopy and definitive resection in group B.

Surgical resection will follow the French national guidelines for GA, published by the SFCD-ACHBT-HAS-INCA [18]. In view of the infiltrative nature of SRC tumours, a total gastrectomy is recommended irrespective of the gastric tumour location. Nevertheless, for small distal tumours, a partial gastrectomy may be considered on a case by case basis whilst safeguarding the usual oncological principles of resection. For Siewert type III tumours of the gastro-oesophageal junction the recommendations for resection will apply apart from the requirement of an 8 cm proximal tumour free resection margin. When resection is extended to the lower oesophagus, either transhiatally or via thoracotomy, the lower oesophagus will be resected en bloc with a lower mediastinal lymphadenectomy. Frozen section analysis of the proximal and distal resection margins will be routinely performed. An enlarged resection to adjacent organs will be performed when necessary to obtain an R0 resection and, when noted, resection of peri-tumoural localised carcinomatosis will also be performed. A D2 lymphadenectomy without distal pancreatectomy and splenectomy will be standard, with the harvest of at least 25 lymph nodes. In both treatment arms the trial protocol recommends the placement of a feeding jejunostomy to limit post-operative weight loss and to help facilitate tolerance of subsequent adjuvant therapy.

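### The group A cytology aim credits chemotherapy with a change that also reflects 12–23 weeks of elapsed time and is seen only in operated patients

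*Protocol article*

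**What the plan says.** All references are to the protocol article.

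- Surgical Resection plans a second cytology at the start of the definitive operation, with one purpose per arm. In group A it is to study the effect of "preoperative chemotherapy on the results of cytology performed during staging laparoscopy in group A". In group B it is to study "the effect on peritoneal cytology of the interval between exploratory laparoscopy and definitive resection in group B".
- The first sample comes from the staging laparoscopy in Pre-therapeutic work-up: "Staging laparoscopy will be performed systematically". On timing, "The initial work-up must take place in the 4 weeks preceding randomisation".
- For group A, "Neoadjuvant treatment will commence within 4 weeks of randomisation and each cycle will last 21 days". There are three such cycles before surgery, and "surgical resection will be performed 3–6 weeks after the completion of neoadjuvant chemotherapy".
- For group B, the section on the adjuvant regimen puts primary resection no later than 4 weeks after randomisation.
- Endpoints of trial lists the prognostic impact of positive cytology as a secondary endpoint. It does not list either before-and-after aim, and it does not say which of the two samples serves the prognostic question.
- No second sample is described for a patient who does not come to resection.

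**The concern.** The group A aim names a cause, preoperative chemotherapy, for a change measured in one arm before and after treatment. Two other things happen between those samples. Time passes, and some patients leave the path to surgery.

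Time is not a neutral background here. The trial's hypothesis, in the abstract and again in the Discussion, is that delaying definitive surgery may let the tumour progress. Reading the group A change as a chemotherapy effect assumes that the delay itself does nothing to the peritoneum, which is the opposite of that hypothesis. Clearance by chemotherapy and progression over time could also offset each other, so the error could go in either direction.

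A published statement that chemotherapy did or did not clear peritoneal cytology would bear on the question the trial was set up to answer, and this sampling scheme cannot support it.

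**Working it through.** The article gives no interval, sample size or expected rate for the cytology work, so there is no stated figure to reproduce. The intervals follow from the windows.

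**Inputs (weeks)**
- Laparoscopy to randomisation, both arms: 0–4 (Pre-therapeutic work-up).
- Randomisation to start of chemotherapy, group A: 0–4 (Peri-operative chemotherapy).
- Three cycles of 21 days, group A: 3 × 21 / 7 = 9.
- End of chemotherapy to surgery, group A: 3–6.
- Randomisation to surgery, group B: 0–4 (Adjuvant chemotherapy regimen).

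**Interval between the two samples**
- Group A, shortest: 0 + 0 + 9 + 3 = 12. Longest: 4 + 4 + 9 + 6 = 23.
- Group B, shortest: 0 + 0 = 0. Longest: 4 + 4 = 8.
- Smallest gap between the ranges: 12 − 8 = 4 weeks.
- If completion of chemotherapy is instead counted from day 1 of the third cycle, group A loses 3 weeks and becomes 9–20. That still lies above 8.

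**What the samples can identify**

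Write C for the chemotherapy effect and T(w) for the change that w weeks would bring without chemotherapy.
- Observed change in A = C + T(12 to 23).
- Observed change in B = T(0 to 8).
- Difference = C + [T(12 to 23) − T(0 to 8)].

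The bracket is zero only if nothing happens to the peritoneum in the extra weeks. Extrapolating from B would have to reach at least 4 and up to 23 − 8 = 15 weeks beyond anything observed there.

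**Selection on reaching surgery**

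The section on discontinuing treatment lists progression, toxicity, refusal and death among the ways a patient may stop the protocol, and group A has much longer for these to occur before surgery. The article gives no rates, so the following is illustration only. Assume 15% are positive at laparoscopy, no patient truly changes, a share d of group A never reaches surgery, and a share q of those lost is positive. Observed positivity at surgery is (0.15 − d × q) / (1 − d).

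| d | q = 15% | q = 40% | q = 60% |
|---|---|---|---|
| 5% | 15.0% | 13.7% | 12.6% |
| 15% | 15.0% | 10.6% | 7.1% |

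Compared with the full baseline of 15%, an apparent fall can arise from selection alone. Pairing each operated patient with his or her own first sample removes this artefact, but the result then speaks only for operated patients.

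**The case against.** The strongest reply is that the article gives one sentence on why a second sample is taken and fixes no analysis set, denominator or test, and that such detail belongs in the full protocol or analysis plan. This stands as far as the analysis method goes. It does not answer the point, because the sentence does fix the sampling moment and the causal label, and no later analysis of these samples alone can separate chemotherapy from elapsed time.

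Three stronger readings are tempting and are not supported.

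- A reader might infer that neither aim can be met. The group B aim asks only about change over group B's own interval. Paired samples over 0–8 weeks without chemotherapy address it directly, and group A's longer interval is irrelevant to it. It remains observational, since interval length is not randomised, and it too covers operated patients only, but the wait from randomisation is at most 4 weeks.
- A reader might infer that patients found with carcinomatosis at surgery give no second sample, from "In cases of the discovery of peritoneal carcinomatosis, peritoneal cytology will not be performed". That rule is written for the staging laparoscopy. At surgery the sample is taken at the start, and the article foresees resecting localised carcinomatosis. Only patients who never come to surgery are clearly unsampled.
- A reader might infer a guaranteed-survival bias in the prognostic analysis, since "OS is defined as the time interval between inclusion and death from whatever cause" and the surgical sample comes later. This arises only if the surgical sample is used for prognosis, which the article does not say.

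It is also fair that the delay hypothesis itself is tested by overall survival in all randomised patients, from which the cytology work removes nobody.

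**Conclusion.** The point holds for the group A aim only. On the stated windows the samples are 12–23 weeks apart in A and 0–8 weeks apart in B, without overlap, so an isolated chemotherapy effect on cytology is not identified. The observed change applies to patients who reach surgery. The interval result assumes that the windows are kept and three full cycles are given.

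How far selection distorts the picture cannot be stated. The article gives neither the share who miss surgery nor their peritoneal status, and the table above only shows what assumed values would do. It should not be read as evidence that peritoneal progression is being hidden.

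Severity is minor. The aim is exploratory, it is not among the listed endpoints, and the primary analysis is untouched.

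**What to change.** 1. Restate the group A aim as the paired change in cytology over chemotherapy plus elapsed time, among operated patients. Keep the group B aim as it is.
2. Report by arm how many patients with a laparoscopy sample have no second sample and, where known, why.
3. Add a between-arm comparison of peritoneal status at planned surgery, adjusted for laparoscopy cytology. In a sensitivity analysis, count non-resection for peritoneal progression as failure, so that patients lost on the way to surgery are not ignored. Describe the result as an effect of strategy (chemotherapy plus delay against prompt surgery). State as a limitation that only group A is formally restaged before surgery, and that this restaging lists no laparoscopy, so peritoneal status in unoperated group A patients is imperfectly known.
4. For prognosis, use the laparoscopy cytology with survival from inclusion. If the surgical cytology is used, count survival from surgery.

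Cost: no new samples, mostly wording and one added analysis. The article does not say outright that the reason for not reaching surgery is recorded, so a data item may be needed. The sponsor gives up the claim to an isolated chemotherapy effect on cytology.
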